# Study protocol for a non-inferiority trial of a blended smoking cessation treatment versus face-to-face treatment (LiveSmokefree-Study)

**DOI:** 10.1186/s12889-016-3851-x

**Published:** 2016-11-24

**Keywords:** Health care sector, Tobacco use disorder, Smoking cessation, Randomized controlled trial, Internet-based-treatment, Blended care, Blended treatment, Online counseling, eHealth

## Abstract

**Background:**

Smoking cessation can significantly reduce the risk of developing smoking-related diseases. Several face-to-face and web-based treatments have shown to be effective. Blending of web-based and face-to-face treatment is expected to improve smoking cessation treatment. The primary objective of this study is to compare the prolonged abstinence rate of the blended smoking cessation treatment with the face-to-face treatment. Secondary objectives are to assess the benefits of blended treatment in terms of cost effectiveness and patient satisfaction, and to identify mechanisms underlying successful smoking cessation.

**Methods/Design:**

This study will be a single-center randomized controlled non-inferiority-trial with parallel group design. Patients (*n* = 344) will be randomly assigned to either the blended or the face-to-face group. Both treatments will consist of ten sessions with equal content held within 6 months. In the blended treatment five out of ten sessions will be delivered online. The treatments will cover the majority of behavior change techniques that are evidence-based within smoking cessation counseling. All face-to-face sessions in both treatments will take place at the outpatient smoking cessation clinic of a hospital. The primary outcome parameter will be biochemically validated prolonged abstinence at 15 months from the start of the smoking cessation treatment.

**Discussion:**

This RCT will be the first study to examine the effectiveness of a blended smoking cessation treatment. It will also be the first study to explore patient satisfaction, adherence, cost-effectiveness, and the clinically relevant influencing factors of a blended smoking cessation treatment. The findings of this RCT are expected to substantially strengthen the base of evidence available to inform the development and delivery of smoking cessation treatment.

**Trial registration:**

Nederlands Trialregister NTR5113. Registered 24 March 2015.

## Background

Killing nearly six million people a year, smoking tobacco is one of the biggest public health threats. Of the smokers who are aware of the dangers of tobacco the majority want to quit [1]. Although a proportion of smokers quit without professional support [2], counseling and medication can more than double the success rate [1]. Success rates of smoking cessation treatments (5-months-after-treatment) range between 8,5% (minimal or no counseling or self-help) and 27,6% (intense counseling & medication) [3], depending on (1) contact time and intensity, (2) number and length of sessions, (3) number and type of clinicians involved, and (4) number and type of counselling formats and interventions. A treatment comparable to the ones of this trial has shown to lead to a cotinine-validated prolonged 12 months’ abstinence rate of 10% (based on intention-to-treat analysis) [4, 5].

Traditionally, smoking cessation treatment is offered as face-to-face counseling. With the rise of the internet, web-based treatment offers an additional channel for effective smoking cessation [6]. Nowadays face-to-face treatment and web-based treatment are usually offered separately. An integration of web-based and face-to-face treatments (blended treatment) is expected to combine the “best of both worlds” [7] as this will allow the strengths of one to offset the weaknesses inherent in the other [8].

The weaknesses of face-to-face treatment that can be offset by the strengths of web-based treatment refer to (1) therapist drift; (2) patients’ no-show and (3) travel costs. (1) Face-to-face treatments often suffer from therapist drift [9]. This drift can be reduced by the protocolled nature of web-based treatments, which have shown to lead to higher treatment integrity [10]. (2) Patients’ no-shows result in time lost both for the counselors and the patients. In BSCT counselors can replace patients not showing up with online work, which can be planned flexibly as the process of online communication with the patients occurs asynchronously. Patients that miss a face-to-face session can still access their personal online dossier and continue treatment autonomously (e.g. psycho-education, exercises, and summaries of counseling conversations). As both counselors and patients can use their time more efficiently this can result in offering treatment to more patients [11]. (3) Travelling to the smoking cessation clinic to attend a face-to-face meeting with the counselors is both time consuming and costly for the client. Web-based sessions do not require showing up at the clinic during the normal business hours, because they can be done e.g. at home in the evening. This reduces work time lost as well as travel related costs for the patients [9, 12].

The weaknesses of web-based treatment that can be offset by the strengths of face-to-face treatment refer to (1) poor engagement of patients and (2) tailoring of interventions. (1) A common problem of web-based treatment is poor engagement of users due to the small amount of personal contact [13]. Face-to-face treatment offers more personal contact and may therefor result in a higher commitment of the patients. (2) Web-based treatments are supposed to offer more tailoring [6]. Face-to-face treatment can offer greater flexibility in customizing interventions to the patients’ needs by for example explaining therapeutic interventions or providing additional information for diagnostic purpose or case management [9, 14, 15].

To the best of our knowledge there has been no research on the potential benefits of a blended treatment for smoking cessation. The primary objective of this research is to find out if a blended smoking cessation treatment (BSCT) results in non-inferior quit rates compared to a face-to-face treatment as usual (TAU). Secondary objectives are to assess whether (1) patients are more satisfied with BSCT; (2) BSCT reduces treatment costs; (3) there is link between quitting and adherence in BSCT; (4) there are moderators or mediators predicting treatment outcome; and (5) how the treatment can further be improved.

## Methods/Design

The study will be a single-centre randomized controlled non-inferiority trial with a parallel group design.

### Study population

The study population will consist of the patients of the outpatient smoking cessation clinic at Medisch Spectrum Twente (MST), Enschede, The Netherlands. These patients will be referred to the clinic by treating physicians of the hospital or by their GPs.

### Inclusion/Exclusion criteria

Participants of this study will be smokers who admit themselves to the cessation clinic (indicating readiness to quit), who are at least 18 years old, who are currently daily smokers (at least one cigarette/day), and who are able to both access websites and communicate by email (both verified during intake procedure by asking whether the participant has internet access at home, and a current email address). People who are not able to read or write in the Dutch language will be excluded from this study.

### Recruitment

Participant will be recruited from those patients that have signed up for smoking cessation treatment at the outpatient smoking cessation clinic. Based on earlier studies and the criteria for participation, we expect that a majority of patients will be eligible for this study. Participation in the study will be voluntary and patients will not receive any payment for participation.

### Randomization

Patients will be randomly assigned to either BSCT or TAU. Randomization will be performed at the individual level (allocation ratio 1:1) using QMinim Online Minimization (http://qminim.sourceforge.net/) [16]. The minimization will be stratified according to: (1) level of internet skills [17]; (2) level of nicotine dependence [18]); and (3) the quitting strategy favored by the patient (stop at once, gradual change, scheduled reduced smoking; for details see below the description of the study intervention). The data used for the QMinim minimization will be collected using the baseline questionnaire, which will be filled in online by the patient at home.

### Blinding

The study will be an open label study, as it is self-evidently impossible (due to the nature of the treatment conditions) to blind the staff and patients that are involved.

### Study intervention

BSCT will be a combination of face-to-face treatment combined with web-based treatment into one integrated smoking cessation treatment that can be delivered in conventional smoking cessation clinics [12, 14]. Both BSCT and TAU will be provided by the Outpatient Smoking Cessation Clinic (SRP), which is part of the Department of Pulmonary Medicine of MST hospital. The web-based interaction of BSCT – which patients will do e.g. at home - will make use of Tactus Addiction Treatment’s website http://www.rokendebaas.nl. Out of this web-based treatment five session have been adopted for the integration in BSCT (Table 1). The SRP team consists of a pulmonologist and three qualified stop-smoking counsellors. The counsellors are registered on the Dutch Quality Register of qualified smoking cessation counsellors (http://www.kwaliteitsregisterstopmetroken.nl). Both treatments fulfil the requirements of the Dutch care module for smoking cessation [19] which is derived from the evidence-based Dutch Guideline Treatment Tobacco Addiction [20]. The costs of smoking cessation treatment will be reimbursed by the patient’s health care insurance.

**Table 1 Tab1:** Distribution of the behaviour change techniques in the face-to-face and online session in BSCT and TAU

Session/week	Name (Code) of the main behavioural change techniques according to [20]	TAU	BSCT
Session 1, week 1 Goal setting	Provide information on consequences of smoking and smoking cessation (BM1) Provide rewards contingent on successfully stopping smoking (BM4) Identify reasons for wanting and not wanting to stop smoking (BM9) Facilitate goal setting (BS4) Prompt self-recording (BS6) Advise on stop-smoking medication (A1) Advise on/facilitate use of social support (A2) Build general rapport (RC1) Explain expectations regarding treatment programme (RC4)	Face-to-face	Face-to-face
Session 2, week 3 Measures for self-control	Provide feedback on current behaviour (BM3) Provide rewards contingent on effort or progress (BM7) Facilitate barrier identification and problem solving (BS1) Facilitate relapse prevention and coping (BS2) Prompt review of goals (BS5) Prompt self-recording (BS6) Advise on changing routine (BS7) Tailor interactions appropriately (RD1)	Face-to-face	Online
Session 3, week 5 Dealing with withdrawal	Provide feedback on current behaviour (BM3) Provide normative information about others’ behaviour and experiences (BM5) Facilitate relapse prevention and coping (BS2) Prompt self-recording (BS6) Provide information on withdrawal symptoms (RC6) Provide reassurance (RC10)	Face-to-face	Face-to-face
Session 4, week 7 Breaking habits	Provide feedback on current behaviour (BM3) Provide normative information about others’ behaviour and experiences (BM5) Facilitate barrier identification and problem solving (BS1) Facilitate relapse prevention and coping (BS2) Advise on changing routine (BS7) Advise on conserving mental resources (BS10) Advise on avoiding social cues for smoking (BS11) Advise on/facilitate use of social support (A2) Provide reassurance (RC10)	Face-to-face	Online
Session 5, week 9 Dealing with triggers	Provide rewards contingent on effort or progress (BM7) Facilitate relapse prevention and coping (BS2)	Face-to-face	Face-to-face
Session 6, week 11 Food for thought	Provide feedback on current behaviour (BM3) Offer/direct towards appropriate written materials (RC5) Elicit client views (RC8)	Face-to-face	Online
Session 7, week 14 Think differently	Provide feedback on current behaviour (BM3) Measure CO (BM11) Facilitate barrier identification and problem solving (BS1) Facilitate relapse prevention and coping (BS2) Prompt self-recording (BS6) Build general rapport (RC1) Elicit and answer questions (RC2)	Face-to-face	Face-to-face
Session 8, week 18 Do differently	Provide feedback on current behaviour (BM3) Facilitate barrier identification and problem solving (BS1) Facilitate relapse prevention and coping (BS2) Prompt self-recording (BS6) Tailor interactions appropriately (RD1) Build general rapport (RC1)	Face-to-face	Online
Session 9, week 22 Action plan	Provide feedback on current behaviour (BM3) Measure CO (BM11) Facilitate action planning/develop treatment plan (BS3) Build general rapport (RC1) Elicit client views (RC8)	Face-to-face	Face-to-face
Session 10, week 26 Closure	Provide feedback on current behaviour (BM3) Provide rewards contingent on successfully stopping smoking (BM4) Strengthen ex-smoker identity (BM8) Facilitate barrier identification and problem solving (BS1) Facilitate relapse prevention and coping (BS2) Facilitate goal setting (BS4) Set graded tasks (BS9) Advise on/facilitate use of social support (A2) Build general rapport (RC1) Offer/direct towards appropriate written materials (RC5) Elicit client views (RC8)	Face-to-face	Online

Codes: BM = Specific focus on behaviour (B) and addressing motivation (M); BS = Specific focus on behaviour (B) and maximising self-regulatory capacity/skills (S); A = Promote adjuvant activities (A); RC = General aspects of the interaction (R) focusing on general communication (C); RD = General aspects of the interaction (R) focusing on delivery of the intervention (D)

TAU is personalized to the patients’ needs and contains flexibility in quitting strategies. To allow for comparability this flexibility is also integrated in BSCT. At treatment start the patients will be asked to favor one of three quitting strategies:Stop at once: the patient sets a quit date, makes a preparation plan and stops abruptly on the quit date.Gradual change: the patient selects daily activities and contexts in which smoking is habitual and step-by-step continues these activities smoke free (for example when reading newspaper, Facebook, reading email, drinking coffee); finally, the patient sets a quit date. Being already accustomed to a range of daily habits without smoking will make it easier for the patient not to relapse.Scheduled reduced smoking [21]: the patient gradually decreases the number of cigarettes at regular intervals; at the start the patient does not smoke less but becomes used to a fixed schedule, and in subsequent phases the number of cigarettes will be gradually reduced (100% → 75%; 75% → 50%; 50% → 25%) until the patient is ready to stop completely. This strategy systematically deconditions the cues. Although recent studies [22, 23] suggest that gradual cessation strategies – such as scheduled reduced smoking - may be sub-optimal compared to abrupt cessation, gradual cessation is still superior to non-treatment [21]. Offering scheduled reduced smoking broadens the target group for the cessation clinic, as it also allows patients who are initially reluctant to quit abruptly to enroll. Further, as it is an established part of TAU in this clinical setting, gradual cessation needs to be included in BSCT as well.

Both BSCT and TAU will consist of ten sessions with similar content spread over 6 months, with the frequency of sessions fading over time (six sessions within the first 3 months, four sessions within the final 3 months). Although participants may choose their preferred quitting strategy, this only marginally affects the content of the actual treatment that is delivered. Regardless of quitting strategy, the number and order of sessions is identical, as well as the effective components: the behavioral change techniques applied within sessions do not vary systematically. However, within the early sessions some differences may occur on a more detailed level within the BCTs (e.g. the timing of goal achievement within goal setting), due to quitting strategy.

All TAU sessions will take place at the SRP clinic while BSCT sessions will take place alternately face-to-face at the SRP (five sessions) and online (five sessions). This blended protocol resulted from a user centered design approach in which experts and counselors were involved in developing the most suitable mix of both delivery modes. The 50–50% blend of face-to-face and web-based sessions results in a considerable substitution by web-based interaction, while at the same time maintaining the intensity of the full intervention.

As in TAU, BSCT consists of both counselor-dependent and counselor-independent components. The counselor-dependent web-based components of BSCT are interactive and rely on (asynchronous) communication between counselor and patient. The counselor-independent components such as psycho-educational content or the smoking diary are used by the patients on their own and in their own time. In TAU these components are provided in a paper manual that clients take home. In BSCT, these components are accessible online. As such, both treatments are equivalent with regard to both content and intensity. An additional benefit of BSCT, though, is that the content of previous counselor-dependent components remains accessible as email correspondence saved online.

Both BSCT and TAU will cover the majority of the behavior change techniques that are used within individual behavioral support for smoking cessation [24], including those techniques that have shown to be reliably associated with better quit outcomes [25]. The distribution of the main behavior change techniques and the distribution of the face-to-face and web-based session are shown in Table 1.

### Measurements

The time-points of the follow-up measurements are tied to the estimated stop-date, which is appropriate for aid-to-cessation trials [26]. The expected stop-date is 3 months after treatment start, which is later than in common cessation treatments where quitting usually is expected within 1 to 3 weeks. In total there will be four follow-up measurements with measurement 3 and 4 (9 and 15 months follow-up) to be conducted at standard time points (i.e. 6 and 12 months after the expected stop-date):3 months after treatment start, expected stop-date, (3 months follow-up);6 months after treatment start, end of treatment and 3 months after expected stop-date, (6 months follow-up);9 months after treatment start, 3 months after end of treatment, 6 months after expected stop-date, (9 months follow-up); and15 months after treatment start, 9 months after end of treatment, 12 months after expected stop-date, (15 months follow-up).

A measurement schedule can be found in Table 2. The biochemical measurements will be done when the patient is at the hospital for a face-to-face session in week 1 (Exhaled CO; baseline/month 0), week 14 (Exhaled CO & Cotinine level; month 3) and week 22 (Exhaled CO; month 5). For the final biochemical measurement (Exhaled CO & Cotinine Level; month 15) which will take place 12 month after the expected stop date in month 3, the patient will have to return to the hospital. All other assessments will be done using online questionnaires which the patients will complete at home.

**Table 2 Tab2:** Measurement schedule

Variables	Measurement at month					
	0	3	5	6	9	15
Primary outcome						
Cotinine level		X				X
Secondary outcomes						
Nicotine dependence (Fagerström)	X			X	X	
MAP-HSS + smoking related complaints of smokers	X			X	X	X
Depression, anxiety and stress (DASS21)	X			X	X	X
Quality of Life (Euroqol 5D)	X			X		
Smoking status	X	X		X	X	X
Adherence						X
Costs						X
Baseline predictors and moderators of treatment effect						
Internet Skills	X					
Readiness to change	X					
Attitude	X			X	X	
Social Influence	X					
Self-Efficacy	X			X		
Alcohol/substance (mis)use	X			X		
Descriptive variables						
Patient characteristics and medical history	X					
Smoking history	X					
Stop Smoking History	X					
Other information of interest						
Evaluation of treatment		X		X	X	X
Exhaled carbon monoxide (CO) level	X	X	X			X

The CO measurements in the study will serve as a backup for the cotinine measurements. They will only be analyzed in case the saliva samples are not usable. This backup strategy has been chosen because CO measurements are part of the routine stop-smoking treatment. To keep the burden for the participating patients as low as possible the measurements are linked to the scheduled face-to-face sessions. As the last face-to-face session in both treatment groups usually takes place in week 22 this moment has been chosen for the measurement to prevent the patient from travel time/work time loss for an extra appointment because of the study.

During the informed consent procedure all participants will receive a patient information letter that outlines the burden of participation, including the online questionnaires. By stressing the importance of the online questionnaires we try to increase patient commitment. During the trial, completion of the questionnaires will be checked after 2 weeks. Participants not completing the questionnaire will receive four weekly reminders: first twice via email, then twice by telephone. If a participant signals to be struggling with completing the questionnaire online, we will offer a paper version of the questionnaire, which will be sent including a return envelope.

## Instruments

### Primary outcome (Cotinine level)

The primary outcome parameter will be biochemically validated prolonged abstinence [26] at 15 months from the start of the smoking cessation treatment. Saliva cotinine level will be measured as biochemical verification of abstinence only by those patients that report quitting smoking in the previous online questionnaires [27]. Prolonged abstinence is defined as having salivary cotinine levels < 20 ng/ml [28] that validate both the self- reported abstinence after the self-chosen stop date – usually 3 months after start - and the self-reported abstinence at 15 month follow-up. Patients not reporting abstinence or with a higher cotinine level on any of these follow-ups will be regarded as smokers as well as patients who are lost to follow-up. A 0,5–1 ml salivary sample will be collected for cotinine assessment by means of a Salivette (Sarstedt AG & Co., Nümbrecht, Germany). Under supervision, patients will have to chew on a cotton swab for 1min to stimulate the saliva flow rate. All saliva specimens will be frozen until assayed and transported to the laboratory for the determination of the cotinine level using a gas chromatography technique.

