### Data management

The handling of personal data will comply with the Personal Data Protection Act in The Netherlands. Data will be recorded using the two ways of data collection described below.Data from the face-to-face contacts will be recorded on data collection forms and centrally collected at Medisch Spectrum Twente. The study data manager will record all the collected data in a Microsoft Access 2007 database.The majority of data will be recorded by Tactus Addiction Treatment – a regional addiction care organization with experience in web-based treatment - using online questionnaires which will be offered to both treatment groups. Individual patients and counsellors will have a login with username and password secured by Secure Sockets Layer to the application. All data transferred between the patient’s personal computer and the application will be encrypted and sent via the https protocol. All data will be encrypted and stored on servers in secure data centres within the Netherlands. Daily backups of the server will be made to ensure further data security.

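### Scoring as abstinent requires an online report of quitting first, so abstinent non-responders become smokers; response may differ by arm, in a direction the protocol does not settle

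*Protocol article*

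**What the plan says.** The section Primary outcome (Cotinine level) restricts cotinine sampling: it is done "only by those patients that report quitting smoking in the previous online questionnaires". On scoring it adds: "Patients not reporting abstinence or with a higher cotinine level on any of these follow-ups will be regarded as smokers". Patients lost to follow-up are treated the same way. Abstinence has to be self-reported and cotinine-validated twice, after the stop date (usually month 3) and at month 15.

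The Measurements section fixes the channel. Saliva and CO are collected in person: "The biochemical measurements will be done when the patient is at the hospital for a face-to-face session" (for month 3, the week-14 session), with a separate hospital return at month 15. For the rest: "All other assessments will be done using online questionnaires which the patients will complete at home".

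The arms differ in how much of the treatment runs on the web: "All TAU sessions will take place at the SRP clinic while BSCT sessions will take place alternately face-to-face at the SRP (five sessions) and online". On the self-help components, Study intervention says: "In TAU these components are provided in a paper manual that clients take home". Data management says that most data are recorded by the addiction-care organisation "using online questionnaires which will be offered to both treatment groups"; the same organisation's website carries the BSCT web sessions.

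There are safeguards. Completion is checked after two weeks, and then: "Participants not completing the questionnaire will receive four weekly reminders: first twice via email, then twice by telephone". A paper version is posted to patients who say they are struggling online. CO serves as a backup to cotinine.

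**The concern.** The rule makes a web form a precondition for counting as a treatment success. A patient who has stopped smoking and attends session 7, but has not answered online, is not sampled and scores as a smoker. That is an ascertainment failure, and the intention-to-treat set does not correct it.

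Two consequences matter in a non-inferiority trial. First, even equal non-response multiplies both abstinence rates by the same factor and so shrinks the absolute difference towards zero, while the 5-point margin stays fixed. Second, the arms have different amounts of web contact after randomization. BSCT patients have three online sessions (weeks 3, 7 and 11) before the month-3 measurement and TAU patients have none, so response among abstainers may differ. Depending on which arm answers less, this either raises the chance of a false non-inferiority claim or costs power.

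**Working it through.** **Inputs from the protocol** (Sample size; Data analysis/Statistical methods): TAU 10%, BSCT 15% expected, margin 5 points, α 0.025, power 80%, 172 per group, 95% confidence interval for the difference.

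**Reproducing the plan's figure.** n per group = (z₀.₉₇₅ + z₀.₈₀)² × [p_B(1−p_B) + p_T(1−p_T)] / (p_B − p_T + margin)². With z values 1.960 and 0.842 this is 7.849 × (0.1275 + 0.0900) / 0.10² = 170.7, so 171. With pooled variance, 7.849 × 2 × 0.125 × 0.875 / 0.01 = 171.7, so 172. The stated size reproduces with one-sided α of 0.025.

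**Model.** Let r_B and r_T be the probability that a true abstainer reports abstinence as the rule requires. The protocol gives no such rates, so every value below is an assumption. Observed rate = true rate × r. With true rates at the margin (5% and 10%), the observed difference is 0.05·r_B − 0.10·r_T:

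- 100/100: 0.050 − 0.100 = −5.0 points
- 80/80: 0.040 − 0.080 = −4.0 points
- 90% BSCT / 80% TAU: 0.045 − 0.080 = −3.5 points
- 80% BSCT / 90% TAU: 0.040 − 0.090 = −5.0 points

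**Chance of declaring non-inferiority.** The binomial probabilities of all pairs of counts (0 to 172 in each arm) were summed over the pairs whose lower 95% limit lies above −5 points. The protocol does not name the interval, so both Newcombe and Wald are shown. Power is at true rates of 15% and 10%.

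| Response BSCT/TAU | False non-inferiority, Newcombe | Wald | Power, Newcombe | Wald |
|---|---|---|---|---|
| 100/100 | 2.4% | 3.1% | 80% | 81% |
| 90/90 | 3.5% | 4.7% | 79% | 81% |
| 80/80 | 5.2% | 7.1% | 79% | 81% |
| 90/80 | 7.5% | 9.8% | 88% | 89% |
| 80/90 | 2.3% | 3.2% | 67% | 69% |

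The 90/80 figure exceeds both equal-response figures (3.5% and 5.2%). Part of the inflation therefore comes from the gap between arms and part from the shrinkage that missing-as-smoker causes on its own.

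**Scale in patients.** At 10%, TAU has 172 × 0.10 = 17.2 true abstainers; 80% response loses 0.20 × 17.2 = 3.4 of them. Because the report is needed at two follow-ups, 90% response at each, if independent, already gives 0.90 × 0.90 = 81% overall.

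**Timing at week 14.** The protocol does not give the send date of the month-3 questionnaire. If it goes out at about week 13 (3 × 52/12 = 13), the two-week check falls at week 15, after the saliva session. The telephone reminders come later still. No other cotinine sample is scheduled before month 15 (Table 2).

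**The case against.** A reader might infer that TAU response will be lower, so that the rule favours BSCT. The documents do not support this.

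- Every participant must have internet access and email (Inclusion/Exclusion criteria). Both arms fill in the baseline questionnaire online at home, and minimization includes internet skills (Randomization).
- The online questionnaires go to both arms, and the patient login in Data management is not limited to BSCT.
- The Background calls poor engagement a common problem of web-based treatment, and Sample size considers BSCT patients who ignore the web part entirely. Such patients might skip web questionnaires too.
- All web sessions end nine months before the month-15 measurement, so any arm difference is less plausible there.

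These points stand, and they leave the direction open. They do not establish equal response: baseline skills and minimization cannot balance web exposure created after randomization, and neither engagement passage is about questionnaire response among abstainers.

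A reader might also infer that an online answer is the only route, or that nothing can be recovered later. That is too strong. There are telephone reminders and a paper form, and the section on exhaled CO allows CO to be used when cotinine is missing. The cover is incomplete, however. Paper is offered only to patients who signal difficulty, and the primary outcome section does not mention it. Measurements words the CO backup more narrowly, for unusable saliva samples. A CO value also does not help a patient who has not reported abstinence, since that patient is a smoker by rule. At month 15 the reminders have time to work, because the sample needs a separate return visit.

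**Conclusion.** The rule misclassifies abstinent non-responders as smokers, and this holds whichever arm answers less. Differential ascertainment is a risk of unknown direction; it is not a demonstrated bias towards non-inferiority. With Newcombe intervals and the assumed response rates, false non-inferiority rises from 2.4% to 5.2% at equal 80% response and to 7.5% at 90% BSCT / 80% TAU. With the gap reversed it stays at 2.3%, and the cost is power, which drops from 80% to 67%. These sizes rest on assumed response among abstainers and on true rates at the protocol's own planning values and margin. With near-complete response the effect is small.

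Handling of study dropouts calls the missing-as-baseline rule conservative. That is true of each arm's abstinence rate, but not of the non-inferiority comparison, even when response is equal.

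**What to change.** - **Week 14:** both arms are in the clinic for session 7 and CO is already measured. Record smoking status on a standard form and take saliva from every self-reported abstainer, whether or not the online questionnaire is in.
- **Month 15:** accept smoking status by online form, paper or the telephone reminder already planned, and invite every self-reported abstainer for the sample.
- **Both arms:** apply the rule identically and report response by arm at each follow-up.
- **Analysis:** drop the claim that missing-as-smoker is conservative for the non-inferiority comparison, and add a sensitivity analysis to that rule.
- **CO backup:** align the two statements of when CO may replace cotinine.

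The cost is some extra saliva assays, one question at an existing visit and in an existing call, and a short amendment; week 14 needs no extra visit. The drawback is that unblinded staff would elicit part of the self-report in an open-label trial. Cotinine verification of each reported abstainer limits that, as does a standard form.
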